**Methods:**

In a randomised controlled trial we will compare (1) brief sex counselling with (2) intensive sexological treatment, and (3) delayed treatment (waiting list). Embedded in this RCT will be a trial-based economic evaluation, looking at the cost-effectiveness and cost-utility of brief sex counselling versus the two other interventions. Four hundred fifty adolescents (aged 18-25) with sexual problems will be recruited among the persons who visit the Public Health Service (PHS) and through various websites. After a screening procedure, eligible participants will be randomly allocated to one of the three intervention groups. Primary outcome measure of the clinical evaluation is the severity of sexual problems. Other outcomes include psychological distress, especially depression. The economic evaluation will be performed from a societal perspective. Costs will be assessed continuously by a retrospective questionnaire covering the last 3 month. All outcome assessments (including those for the economic evaluation) will take place via the internet at baseline, and at 3, 6, 9, and 12 months after baseline.

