### Interventions

#### Brief sex counselling

Brief sex counselling is a brief, free of charge and easily accessible treatment for sexual problems of people between 18 and 25 years of age. In a maximum of three sessions, of 45 minutes each, a sex counsellor attempts to solve the problems or refers to more specialized help. The treatment is aimed at people without relationship and/or psychiatric problems. The sessions include providing information, psycho-education and limited advice on behaviour change. Furthermore home exercise assignments can be given, and the experiences with these exercises are discussed. The possibility for adolescents to talk about their sexuality in a non-threatening environment could initiate the problem-solving process.

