#### Intensive sexological treatment

In a maximum of 10 treatment sessions a (Dutch Association for Sexology) certified sexologist offers an intensive form of treatment for the sexual problem(s) of the participant. This is the standard format of care for adults with sexual problems. In contrast to brief sex counselling, intensive sexological treatment also addresses the relational and/or personal psychological problems which possibly underlie the base of the sexual problems. The treatment is largely based on cognitive-behavioural therapy. In many cases homework assignments have to be carried out. The participant is taught to recognize and change thoughts which could play a negative role in their sex life.

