#### Delayed treatment

In the event of the participant being randomized into the waiting list, a period of 26 weeks follows in which no treatment is offered. Participants are requested not to engage in other types of professional treatment. At the end of the waiting list period the participant can choose between brief sex counselling and the intensive sexological treatment.

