### Outcome measures

Several instruments will be used to assess the effects of brief sex counselling on sexual functioning, depression and other psychological and physical complaints, and on secondary outcomes. Furthermore instruments will be used to assess the cost-effectiveness of brief sex counselling from a social perspective. The outcomes will be measured before randomization (during initial screening), at baseline and at 3, 6, 9 and 12 months after baseline (Additional file 1).

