### Randomisation and procedure

For this study a block randomisation procedure will be used to ascertain that each intervention runs in equally large groups. Although the order of the interventions varies randomly within each block, a person running the trial could deduce some of the next treatment allocations if they discovered the block size. In this study we use larger block sizes (30) and randomly vary in block size which can ameliorate this problem [55]. Allocation will be performed by a central independent research assistant after getting informed consent, screening, and checking the in- and exclusion criteria, using Schouten's (1995) adaptive biased urn randomization for small strata. This keeps randomization unpredictable up to and including the last participant on each site, while keeping the group sizes at each site in good balance [56].

The questionnaires will be administered using a computer. All assessments will take place at home via internet. Preceding an upcoming assessment point, participants will receive an email (one week before the end of the treatment and 3 months after the start of the follow-up measurement). If a participant fails to complete the assessment within one week, an email-reminder will be sent. When the participant fails to fill in the questionnaires, a phone call will be made.

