### Analyses

#### Clinical analyses

Our primary (base-case) analyses will be performed according to the intention-to-treat principle, including data from all participants regardless of whether they received the intervention or not. For the analyses we will use SPSS statistical software and Excel (for the bootstraps). Respondents for whom at least 75% of the data per measurement instrument are available will be included in the analysis. Missing data on item level will be handled using SPSS missing value analysis. Completely missing measurements will be handled using multiple imputation. Analysis will include comparisons of the intervention groups (brief sex counselling, sexological treatment and waiting list) as well as more complicated multi-level analysis. The accuracy of the findings will be expressed in terms of 95% confidence intervals.

To test the main research questions, difference scores for all outcome variables will be calculated and compared between the three intervention groups using MANOVA. In the case of significant multivariate results, subsequent univariate analysis using independent groups t-tests will be conducted to assess the significance of differences pre/post intervention between control and experimental groups.

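### The assessment e-mails are timed from the end of treatment, which conflicts with the fixed schedule of months 3, 6, 9 and 12 from baseline; the post visit in the main comparison is not named

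*Protocol article*

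**What the plan says.** The schedule is given twice on a calendar basis, with no difference between arms. The abstract (Methods) says that all outcome assessments, including the economic ones, "will take place via the internet at baseline, and at 3, 6, 9, and 12 months after baseline". The Outcome measures section says: "The outcomes will be measured before randomization (during initial screening), at baseline and at 3, 6, 9 and 12 months after baseline".

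Randomisation and procedure gives another rule. It opens with "Preceding an upcoming assessment point, participants will receive an email" and puts the timing in a parenthesis: "participants will receive an email (one week before the end of the treatment and 3 months after the start of the follow-up measurement".

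The arms differ in length:
- Brief sex counselling: "In a maximum of three sessions, of 45 minutes each, a sex counsellor attempts to solve the problems".
- Intensive sexological treatment: "In a maximum of 10 treatment sessions a (Dutch Association for Sexology) certified sexologist offers an intensive form of treatment".
- Delayed treatment: "a period of 26 weeks follows in which no treatment is offered", after which participants choose one of the two treatments.

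The Clinical analyses section compares difference scores between the three groups by MANOVA, followed by t-tests "to assess the significance of differences pre/post intervention between control and experimental groups". It names no month as the post measurement.

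**The concern.** An invitation tied to the end of treatment implies an assessment at that point and a follow-up clock that starts there. Where treatment lengths differ by arm, that clock starts at a different time since baseline in each arm. A difference score would then mix the effect of treatment with elapsed time, and randomisation does not remove that.

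The waiting list has a further problem, because it has no treatment to end during its 26 weeks. Staff could take the trigger to mean the end of the wait, or the end of the treatment chosen afterwards. On the second reading controls would be measured after being treated, and the first effectiveness question is brief counselling against delayed treatment.

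The economic evaluation is exposed too. According to the abstract, costs are collected by a questionnaire that looks back 3 months. That covers the year without gaps only if assessments are 3 months apart.

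**Working it through.** The document gives no figure on this point to reproduce. The check is whether the two timing rules can coincide.

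**Inputs.** Maximum sessions: 3 and 10 (the two intervention sections). Waiting period: 26 weeks (Delayed treatment). Visits at 3, 6, 9 and 12 months, which are weeks 13.0, 26.1, 39.1 and 52.2. The interval between sessions is not given; 1 to 4 weeks is my assumption.

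**Step 1: end of a full course.** Weeks from first session = (maximum sessions − 1) × interval.

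| Assumed interval (weeks) | Brief: 2 × interval | Intensive: 9 × interval | Gap: 7 × interval |
|---|---|---|---|
| 1 | week 2 | week 9 | 7 weeks |
| 2 | week 4 | week 18 | 14 weeks |
| 3 | week 6 | week 27 | 21 weeks |
| 4 | week 8 | week 36 | 28 weeks |

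The gap is 7 × interval, so with a common interval two full courses never end together. In this range brief counselling always ends before the month-3 visit (week 13.0). Both session counts are maxima, so end dates would also vary within each arm.

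**Step 2: what would reconcile the rules.** For both active arms to end at month 6, brief sessions would have to be 26.1 / 2 = 13.0 weeks apart and intensive sessions 26.1 / 9 = 2.9 weeks apart. For both to end at month 3, the spacings would be 13.0 / 2 = 6.5 and 13.0 / 9 = 1.4 weeks. The document states no such spacing.

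**Step 3: cost recall.** Suppose treatment starts at baseline and the first follow-up questionnaire comes at the end of treatment. A 13-week look-back from week 26 (waiting list) reaches week 13 and leaves weeks 0 to 13 uncovered. From week 36 (intensive, 4-week interval) it reaches week 23 and leaves weeks 0 to 23 uncovered. From week 8 (brief, 4-week interval) it reaches 5 weeks before baseline and overlaps the earlier period. On the calendar schedule none of this arises.

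**Step 4: does the analysis section settle it?** No. A comparison before and after intervention fits an end-of-treatment measurement at least as readily as a fixed month.

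**The case against.** The strongest reply is that the calendar schedule is the plan. It appears twice, in agreement and without any difference by arm, and the 3-month cost recall fits only that grid. The conflicting text is a parenthesis about notification e-mails. It names two e-mail times for four follow-up visits, so it may simply be loose. The e-mail is advance notice, so week 25 on the waiting list would be an e-mail date and not a measurement date. A benign reading also exists: 26 weeks is the month-6 visit and 3 months later is month 9, both on the grid. Additional file 1 and Figure 1 are not shown and might resolve the matter.

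Much of this stands. A reader might infer that the arms will be measured at different times; the document does not support that, only that they could be if the e-mail rule were followed. The benign reading works for the waiting list, but Step 2 shows that it does not extend to the active arms without session spacings that the text does not give. In the text shown, the two rules remain unreconciled.

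A reader might also infer that baseline answers are given after allocation is known, because Outcome measures lists baseline separately from the measurement before randomisation. No text says so. Allocation follows consent, screening and eligibility checks, and a measurement before randomisation is planned.

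**Conclusion.** The point holds as an internal contradiction that should be corrected: two stated timing rules that cannot both be followed in all arms, and a main comparison that does not say which visit it uses. If the e-mail rule governed, full courses in the two active arms would end 7 to 28 weeks apart. That range rests on the assumed interval of 1 to 4 weeks, the same in both arms.

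The size and direction of any bias cannot be determined from the document. A reader might infer a definite bias against brief counselling. For example, assume measurement at week 8 for brief counselling and week 25 for the waiting list, with linear untreated improvement of 0.1 to 0.3 SD over 26 weeks. Then (25 − 8) / 26 = 0.654, and 0.654 × 0.1 = 0.07 to 0.654 × 0.3 = 0.20 SD, up to half of the planned d = 0.40. The document supports neither the figure nor its sign. Week 8, the rate of improvement and linearity are all assumed. The protocol itself expects problems to escalate without help (Background; second effectiveness question), and if untreated problems worsen the sign reverses.

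**What to change.** 1. In Randomisation and procedure, send all invitations for months 3, 6, 9 and 12 from one common anchor, with the same window in all three arms, as Outcome measures already implies. Delete the end-of-treatment trigger.
2. In Clinical analyses, name the fixed calendar visit that serves as the post measurement, the same in all arms.
3. As a minor safeguard, if the baseline questionnaire is not completed before allocation is disclosed, use the planned screening measurement before randomisation as the pre value.

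The cost is a change to the e-mail schedule and a few sentences. No assessment is added and the sample size is unaffected.

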### Recruitment

Participants will be recruited through different routes; referrals from Rotterdam-Rijnmond PHS, southern South-Holland PHS, Hollands-middle PHS, Maastricht/Heerlen PHS, Sense, and various websites. Adolescents who visit the PHS for a STI or Sense consult, and who report sexual problems, will be asked if they are interested in participating in the study. Adolescents who visit websites providing sexual information, like http://www.sense.info, can click on a banner if they are interested to participate. After thus reporting their interest, they receive an email containing information about the study protocol, and an informed consent (IC) form. Adolescents who return their signed IC form receive login codes for the questionnaires on the internet. Participants who score above the cut-off score on the QSSD and IIEF/FSFI, and meet the inclusion criteria are included in the study. Participants who do not meet the inclusion criteria are offered suitable alternative treatment options.

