### Participants

The patient population we aim to investigate consists of adolescents with sexual problems. Patients are eligible to participate if they meet the following criteria: age between 18 and 25 years old; at least mild to moderate sexual problems (based on Questionnaire for the Screening of Sexual Dysfunction [29,30], International Index of Erectile Function (men) [31] and Female Sexual Functioning Index (female) [32]); no severe psychiatric co-morbidity or relational problems, and the sexual problems are not caused by disease, medication use or physical disabilities.

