#### Sexual functioning

##### Questionnaire for the Screening of Sexual Dysfunctions

The Questionnaire for the Screening of Sexual Dysfunctions (QSSD) [29,30] is a self-report instrument with 70 items, each assessed using a 5-point or a 7-point Likert-scale, which aims to measure the presence (and level) of sexual difficulties. This instrument has different versions, dependent on gender, partnered status and gender of the partner. Anchor points used are 'almost never' and 'always' for frequency and 'no trouble' and 'very much trouble' for associated distress.

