##### Female Sexual Functional Index

The Female Sexual Functional Index (FSFI) [32] is a multidimensional self-report instrument with 19 items, with responses assessed using a 6-point Likert-scale, which aims to measure sexual functioning on the dimensions of sexual desire, arousal, lubrication, orgasm, satisfaction and pain. High score indicates healthy sexual functioning. Its sound psychometric properties have been proven [35].

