##### International Index of Erectile Function

The International Index of Erectile Function (IIEF) [31] is a multidimensional self-report instrument with 15 items, assessed using a 6-point Likert-scale, meant to measure male sexual functioning on the dimensions of erectile functioning, orgasmic functioning, sexual desire, intercourse satisfaction and overall satisfaction. A high score indicates healthy erectile functioning. Its sound psychometric properties have been proven [31].

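### The entry rule asks for scores above the cut-off on the FSFI and IIEF, where high scores mean healthy functioning, so on those two scales it contradicts the eligibility criterion

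*Protocol article*

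**What the plan says.** Three parts of the protocol article bear on this point.

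- **Recruitment** gives the operational rule: "Participants who score above the cut-off score on the QSSD and IIEF/FSFI, and meet the inclusion criteria are included in the study". People who do not meet the inclusion criteria are offered other treatment options.
- **Participants** gives the eligibility criterion. It requires "at least mild to moderate sexual problems", judged on the QSSD, the IIEF (men) and the FSFI (women), alongside criteria on age, co-morbidity and cause.
- **Outcome measures** describes the scales. The QSSD is an instrument "which aims to measure the presence (and level) of sexual difficulties". For the FSFI: "High score indicates healthy sexual functioning". For the IIEF: "A high score indicates healthy erectile functioning".

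The Abstract adds: "Primary outcome measure of the clinical evaluation is the severity of sexual problems". The three scales are the instruments listed under Sexual functioning, so they serve both as the entry screen and as measures of effect.

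**The concern.** A cut-off rule needs a value and a direction. The article gives no values, so the direction is the only operational content a reader or programmer can take from the Recruitment sentence. That direction is the same for three scales that do not all run the same way.

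The rule decides who is randomised. Screening is by internet questionnaire, where a scored rule is easily coded as printed. If that happened, people whose FSFI or IIEF score shows a problem would be turned away. Those admitted would start on the healthy side of the cut-off on that scale, with less room to show improvement. Selection at entry cannot be undone in the analysis.

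**Working it through.** No arithmetic applies: the point concerns the direction of a threshold and depends on no sample size, power or effect size. The check sets the article's own statements side by side.

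| Scale | What a high score means | Where 'above' falls | Side the Participants section needs |
|---|---|---|---|
| QSSD | More difficulty (inferred) | Problem side | Problem side |
| FSFI (women) | Healthy functioning (stated) | Healthy side | Problem side |
| IIEF (men) | Healthy functioning (stated) | Healthy side | Problem side |

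**Step 1: the QSSD.** The article does not say outright that a higher total is worse. It follows from what the instrument measures and from distress anchors that run from none to a great deal. On that inference, 'above' is the right word for this scale.

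**Step 2: the FSFI and IIEF.** Their directions are stated, so no inference is needed. Above the cut-off is the healthy side.

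**Step 3: the conflict.** The eligibility criterion needs a problem on these instruments. The Recruitment sentence asks for the opposite side on the FSFI and IIEF. This does not depend on Step 1. If the QSSD also ran from worse to better, 'above' would be wrong on all three scales.

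**Step 4: who passes the printed rule.** Take a woman; the same holds for a man with the IIEF.

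- *Problem range on both QSSD and FSFI.* She plainly fits the Participants criterion but fails the printed cut-off clause on the FSFI.
- *Problem range on the QSSD, healthy range on the FSFI.* She passes the cut-off clause. Whether she also meets the Participants criterion depends on how the instruments are meant to combine.
- *Healthy range on the QSSD.* She fails the cut-off clause, whatever her FSFI score.

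The person who most clearly belongs in the trial is thus the one whom the literal wording leaves out.

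**Step 5: is there text that rescues the wording?** No section says that the FSFI or IIEF is reverse-scored, or defines 'above' as 'worse than'. Two other places confirm that direction has to be stated scale by scale. The economic analysis counts an increase in sexual functioning as a gain, which agrees with high being healthy. The description of the SEAR says that its high scores indicate problems, so the article uses scales running both ways.

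**The case against.** The best defence is that the intent is obvious. The Abstract and the Participants section define the population as young people with sexual problems. The Recruitment sentence itself requires the inclusion criteria, and Randomisation and procedure has the criteria checked before allocation. The natural reading of 'above the cut-off' is 'in the problem range'. The article condenses a fuller procedure, and nothing in it shows that the screening algorithm uses the wrong direction.

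Much of this stands, and it limits what may be concluded. Three stronger inferences are tempting but not supported.

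- *The trial would test the wrong population.* This ignores the second half of the entry sentence. With the inclusion criteria applied as well, the literal text is self-contradictory; it does not certainly enrol unaffected people.
- *No participant would be impaired on the FSFI or IIEF, where the plan intends all to be.* The first part applies one clause and drops the other. The second assumes that the Participants section demands impairment on every instrument, whereas it says only that problems are judged on them.
- *Two severity measures would sit at a ceiling.* No cut-off values are given, and being above a cut-off is not being at the maximum. Each participant completes only one of the two scales, and the QSSD remains a measure for everyone.

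The defence does not remove the error. The complaint is not that detail was left out: the article states a direction, and for two scales states it wrongly.

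It could also be argued that a correction requiring a problem on the QSSD and on the FSFI or IIEF is too strict, since the counselling protocol covers sexual pain and the IIEF dimensions listed do not. But that conjunction is the Recruitment section's own, and correcting the direction does not alter it.

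**Conclusion.** The entry rule is wrong as written. For the FSFI and IIEF it points to the healthy side of the cut-off and contradicts the eligibility criterion. The contradiction rests only on statements in the article and is certain. That 'above' is right for the QSSD is an inference from its content and anchors.

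The most likely explanation is loose wording. The practical harm is conditional: it arises only if the online screening follows the printed direction, which the article does not reveal. In that case people in the problem range of the FSFI or IIEF would be turned away, and those admitted would have reduced headroom on that one scale. Neither effect can be quantified without the cut-off values and the distribution of screening scores. The point still deserves correction, because an enrolment threshold should be executable as printed.

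**What to change.** Reconcile the Recruitment section with the Participants section and the FSFI and IIEF descriptions by stating the problem side of the cut-off for each instrument. For example: participants are included if they score above the cut-off on the QSSD and below the cut-off on the FSFI (women) or the IIEF (men), and meet the other criteria. Confirm, and state in the QSSD description, that a higher QSSD score is worse. Keep the plan's own way of combining the instruments.

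Then check that the online screening algorithm uses these directions. If screening has already begun, check the stored screening scores against the corrected rule.

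The cost is one sentence and one check of the screening algorithm. Design, sample size and analysis are unchanged.
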